### Randomisation and blinding

The trial pharmacist (un-blinded) will generate a randomisation code using a computer-derived permuted block with varying block size sequence. Manufacturing and preparation of the medication capsules will be performed by an external good manufacturing practice-accredited facility. The unblinded pharmacist will be involved in the preparation of the medication kits as per the randomisation schedule. The sequence will follow a 2 × 2 sequential design whereby participants will receive PGB first, then GBP (or vice versa), in a double-blinded fashion. Owing to the variability in regular dosage frequency between the medications (PGB twice daily, GBP thrice daily), study medication packs will contain three bottles each, correlating to the dosage times of morning, lunchtime and night, so as to maintain blinding. Medication packs pertaining to the PGB arm will have placebo incorporated as the lunchtime dose with all medications being indistinguishable. The randomisation schedule will remain concealed from other researchers. Placebo capsules will have an appearance identical to the active capsules. The randomisation process will ensure concealed allocation and blinding of the specialist, the participant and the outcome assessor.

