### Study treatment

Participants will be randomised to commence treatment on either PGB or GBP. As a result of the cross-over methodology, participants will have the opportunity to experience both PGB and GBP, and we predict little or no carry-over effects (medium- or long-term) after the washout period. We believe the incorporation of a stand-alone placebo arm is unethical in trials where participants with moderate to severe pain are recruited.

The starting dose of PGB is 150 mg once daily for the first week. This will be titrated to the participant’s optimal dose up to a maximum of 300 mg twice daily, depending on their progress and tolerance at each dose level. The starting dose for GBP is 400 mg once daily for the first week. This will be titrated to the participant’s optimal dose up to a maximum of 800 mg thrice daily, depending on their progress and tolerance at each dose level. These doses are based on national recommendations from the Australian Medicines Handbook [11]. In the standard study dosing regimen (Table 1), we expect a 4-week titration period, after which the maximum tolerated dose for each participant will be maintained for 4 weeks before the first study medication is ceased in preparing for washout. The washout period between treatment phases will last 1 week, which is sufficient for these medications because they possess a short half-life (5–7 h). The dosage of either PGB or GBP can be amended at any stage in PAGPROS on the basis of efficacy and/or SEs by communication between the study specialist and the study pharmacist. The maximum treatment period is 8 weeks [13].

**Table 1 Tab1:** PAGPROS medication titration schedule

	Medication	Total daily dose
Week	Pregabalin	
1	1 × 150-mg capsule in the morning	150 mg/day
2	1 × 150-mg capsule three times daily (middle dose is placebo)	300 mg /day
3–8	2 × 150-mg capsules three times per day (middle dose is placebo)	600 mg/day
Week	Gabapentin	
1	1 × 400-mg capsule in the morning	400 mg/day
2	1 × 400-mg capsule three times per day	1200 mg/day
3–8	2 × 400-mg capsules three times per day	2400 mg/day

*PAGPROS* Pregabalin and Gabapentin Prospective Clinical Trial for the Treatment of Sciatica: A Randomised, Double-Blind, Cross-over Study

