### Data collection

Data collection will be conducted by the study researchers via telephone, email or online at baseline (before medication commencement) and at weeks 4, 8, 10, 14 and 18. Week 10 data collection will act as the cross-over secondary baseline for analysis purposes. Data will be entered into CRFs by dedicated trained staff. Each participant will receive up to seven face-to-face or telephone consultations with the trial pharmacist to commence treatment, monitor progress and adjust the dose of the study medication over the 8-week treatment periods. These visits will also incorporate a medical evaluation and collection of primary and secondary outcomes. Participants will receive usual neurosurgical care independent of and parallel to PAGPROS.

The use of prior and continued analgesic medicines will be collected at baseline. Adherence to study medication will be documented through a self-reported daily medication diary and by counting the returned medicine compared with the prescribed regimen as recorded by the trial pharmacist. Participants will be asked to return used and unused study medications at each visit.

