### Data integrity and analysis

The integrity of trial data will be monitored by regularly scrutinising data files for omissions and errors. We will perform double data entry of the primary and key secondary outcomes. The source of any inconsistencies will be explored and resolved. Electronic data will be stored on a secure server, and paper copies will be locked in a cabinet. Data will be accessible only by researchers, and participant confidentiality will be maintained through secure password-protected data storage during and after PAGPROS.

Data will be de-identified prior to statistical analysis, which will be performed on an ITT basis. Normality of data distribution will be assessed, and appropriate parametric (Student’s *t* test or analysis of variance) or non-parametric (Wilcoxon signed-rank test, Wilcoxon rank-sum tests) tests for between-group differences will be performed. Statistical significance will be assessed at *p* < 0.05. Subgroup analysis may be implicated and considered as PAGPROS develops. Time-to-event analysis will be undertaken using Kaplan-Meier estimates on the week 8 and week 18 VAS scores. Missing data will be handled by a single imputation method whereby the last observation will be carried forward and used as a surrogate for the missing value. This method is the favoured approach for replacing missing data because it is conservative, yields an appropriate estimate of variation in outcome and is unlikely to bias towards the alternative hypothesis [15]. An alternative approach to missing data may be use of a longitudinal mixed-effects model incorporated into the analyses.

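### Last observation carried forward is fixed as the missing-data method because it is said to be conservative; in this 2×2 cross-over that justification cannot be relied on

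*Protocol article*

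**What the plan says.** All references are to the protocol article.

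- **Method.** Data integrity and analysis states: "Missing data will be handled by a single imputation method whereby the last observation will be carried forward and used as a surrogate". It calls this the favoured approach "because it is conservative, yields an appropriate estimate of variation in outcome and is unlikely to bias towards the alternative hypothesis".
- **Alternative.** The next sentence makes a model optional: "An alternative approach to missing data may be use of a longitudinal mixed-effects model incorporated into the analyses".
- **Visits.** Under Data collection, outcomes are taken "at baseline (before medication commencement) and at weeks 4, 8, 10, 14 and 18". Weeks 4 and 8 belong to the first drug and weeks 14 and 18 to the second. Of week 10 it says: "Week 10 data collection will act as the cross-over secondary baseline for analysis purposes".
- **Washout.** Under Study treatment: "The washout period between treatment phases will last 1 week".
- **Who goes missing.** Study treatment removes patients who cannot tolerate the starting dose, while keeping them in the intention-to-treat analysis, and withdraws those who need another pain intervention. Adverse experiences and monitoring withdraws those with a serious event suspected to be drug-related. Sample size assumes 20% drop-out.

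Nothing in the article confines carrying forward to the period, or to the drug, in which the value was observed.

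**The concern.** The three properties claimed for LOCF are general assertions. They are not derived for a design in which the last observation may belong to the other drug or to no drug. Reading the rule against the visit schedule gives two cases:

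- **Last seen at baseline, week 4 or week 8.** If the value crosses the washout, it fills both week 8 and week 18. The patient's paired difference is exactly zero, whatever the drugs do.
- **Last seen at week 10.** The second-baseline score becomes the week-18 result of a drug the patient has barely taken. On the Sample size figures (7.5 before treatment, 3.0 on gabapentin), that charges about 4.5 points to the drug that was stopped.

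The reasons for withdrawal are tied to treatment, and a difference in side effects between the drugs is the secondary objective. Equal drop-out by drug therefore cannot be presumed. With 38 patients, a handful of such imputed scores can move a co-primary result, and the stated justification would lead a reader to trust it.

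**Working it through.** **Inputs from the article.** Means 7.5 to 3.0 on gabapentin (GBP) and 7.5 to 2.1 on pregabalin (PGB); difference 0.9; SD 1.2; alpha 0.05 (two-sided assumed); 30 evaluable, 38 in total; 20% drop-out. The Discussion cites an earlier GBP cohort in which 31% stopped within a week.

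**Assumed, not in the article.** Timing of drop-out and its split by drug; the 10% rate for PGB; drop-out at random within sequence; between-patient SD 1.0; mean VAS at week 10 of 7.5 (full return of pain) or 5.0.

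**Step 1: the plan's own figure.** Reading 1.2 as the within-patient SD, N = 2 × [1.2 × (1.960 + 0.842) / 0.9]² = 27.9 by the normal approximation. With the noncentral t, N = 30 gives 80.1% power. Then 30 / 0.8 = 37.5, so 38. The sample size reproduces and is not in question here.

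**Step 2: lost in period 1, value carried across the washout.** Each such patient contributes zero, so the estimate is 0.9 × (1 − d), where d is the drop-out share:

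- d = 0.20: 0.9 × 0.80 = 0.72
- d = 0.31: 0.9 × 0.69 = 0.62

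Simulation (8,000 trials, 19 per sequence, period-adjusted t test) at d = 0.20, for loss after week 8:

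| | LOCF | Complete pairs |
|---|---|---|
| Mean estimate, true difference 0.9 | 0.72 | 0.90 |
| SE, no true difference | 0.244 | 0.307 |
| Type I error | about 5% | about 5% |
| Power | about 81% | about 81% |

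The LOCF SE is below even the 0.273 obtained with no drop-out at all. The imputed zeros count as data. Estimate and SE shrink together, so the test is almost unaffected, but the estimate and its confidence interval are wrong.

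**Step 3: lost early in period 2, week-10 score carried.** Let f and g be the shares of all participants whose PGB or GBP endpoint is replaced by a week-10 mean W, and let T be the treated mean. With no true difference (T = 3.0), the bias in PGB − GBP is (W − T)(f − g).

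Suppose 31% stop GBP and 10% stop PGB, each among the half who take that drug second. Then g = 0.155, f = 0.05 and f − g = −0.105. Overall drop-out is (31 + 10)/2 = 20.5%, close to the planned 20%.

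- W = 7.5: 4.5 × (−0.105) = −0.47 points; simulated type I error about 21%
- W = 5.0: 2.0 × (−0.105) = −0.21 points; simulated type I error about 10%

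Exchange the two rates and the sign reverses. With f = g the bias is zero.

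Under the planned difference and W = 7.5, the contrast is −0.9 + 5.4f − 4.5g. Taking splits of 30% and 10%:

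- More stop PGB (f = 0.15, g = 0.05): −0.9 + 0.81 − 0.225 = −0.315; rejection about 12%
- More stop GBP (f = 0.05, g = 0.15): −0.9 + 0.27 − 0.675 = −1.305; rejection about 87%

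**Step 4: variance in the period-2 case.** With balanced 20% loss after week 10, the LOCF SE is 0.40 against 0.308 for complete pairs when W = 7.5 (about 30% larger). When W = 5.0 it is 0.303, about the same as complete pairs. The error in the SE therefore depends on when patients leave and how far pain returns.

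**Benchmark.** In the same random drop-out scenarios, complete pairs give about 0.90 under the alternative, 0.00 under the null, and type I error near 5%.

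**The case against.** Several points on the other side carry weight.

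- **LOCF is partly what the article says.** Loss in period 1 pulls the estimate towards the null and leaves type I error and power almost unchanged. A reader might infer that all three claimed properties fail in every case, or that LOCF always shrinks the variance. Neither follows: the first case is biased towards the null, and the second can enlarge the SE.
- **The false-positive figures are built on assumptions.** The 31% comes from a single-drug cohort of first use and is placed wholly in period 2. The 10% has no source. The Background reports, on weak evidence, that the two drugs' side effects are probably similar. If the number of drop-outs is fixed at 6 versus 2 instead of varying at random, type I error is about 13% (week-10 score 7.5) or 8% (5.0). These are smaller, but still above 5%.
- **Carrying across periods is not stated.** Using week 10 as a second baseline suggests period-specific change scores, and a full analysis plan may restrict the rule. Change scores do not remove the problem, though. A patient who leaves after week 8, with that value carried to weeks 10 and 18, is credited with zero change on a drug never taken. A restriction to within period would remove the period-1 case but not the week-10 case.
- **The estimand.** If more patients cannot stay on one drug, giving them an off-drug score may reflect a real difference in effectiveness. That would be a defensible choice if the article made it. It instead presents LOCF as a conservative stand-in for the missing value.
- **Whether week 10 is off drug.** A 1-week washout after week 8 ends at week 9. Treating week 10 as untreated rests on its role as second baseline; these passages should be reconciled.

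What stands is that the article gives a reason for LOCF which its own design does not support.

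**Conclusion.** The concern holds in a limited form. The article commits to LOCF, and its justification cannot be relied on in this cross-over.

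Loss in period 1, if values cross the washout, attenuates 0.9 to about 0.72 at 20% drop-out with an SE about 20% too small; the test itself remains valid. Loss early in period 2 distorts the SE by an amount that depends on week-10 pain. When it differs by drug, it biases the contrast either way: 0.2 to 0.5 points and about 10% to 21% type I error under an assumed 31% versus 10% split with week-10 VAS 5.0 to 7.5. With drop-out balanced by drug there is no bias under the null.

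A reader might go further and conclude that this trial will report a false difference. The documents do not support that, because they give neither drop-out timing, nor its split by drug, nor week-10 pain. The supportable conclusion is that the direction and size of the error cannot be known in advance, so the method cannot be called conservative.

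**What to change.** 1. Make the mixed-effects model the primary analysis: all observed VAS and ODI values, fixed effects for treatment and period (and visit, if all visits are used), a random participant effect, and no imputation.
2. Delete the sentence calling LOCF conservative.
3. If LOCF is kept, label it a sensitivity analysis and state that no value is carried across the cross-over.
4. Add a sensitivity analysis for drop-out related to side effects or lack of effect. The mixed model assumes data missing at random, and the withdrawal rules make that assumption open to doubt.

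The cost is analysis wording plus one further sensitivity analysis. The model is already named in the article, and neither data collection nor sample size changes. Patients lost in period 1 will add little to the within-patient contrast, which is an honest reflection of what they can tell us.

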### Sample size

We hypothesise that over an 8-week treatment period, GBP will reduce pain on the VAS scale by an average of 4.5 points from (7.5 to 3.0) as per historical literature [16]. We predict PGB to show at least the same benefit. We hypothesise that PGB will display superiority over GBP by at least a 20% better relative reduction in VAS score, with a resultant reduction of 5.4 (from 7.5 to 2.1) points from baseline. This 20% relative reduction is based on the average reduction of pain symptoms compared with placebo for indirect comparisons [1, 16]. Relative reduction will be used because it is often more impressive and also to allow for the instance of a lower-than-expected event rate, which would lower the absolute risk reduction.

If the true difference in means of both arms of the study is 0.9 with an SD of 1.2, in order to detect this 20% relative decrease in pain between GBP and PGB, we will need to study 30 patients (15 per treatment arm) to reject the null hypothesis with 80% power. The type I error probability associated with this test of the null is 0.05. Assuming a 20% drop-out rate, the total sample size will be 38 patients (19 per treatment arm). We have chosen this large effect size and conservative SD on the basis of anecdotal and specialists’ experience with this cohort of patients. The benefits of the cross-over methodology are evident with the small sample size required, owing to each participant acting as his/her own control. If this were a conventional parallel study design, the sample size needed would be approximately 100 participants. We conservatively estimate that if two people can be recruited per week, the study duration will be approximately 1.5 years.

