### Objectives

#### Primary objective and outcome

Our primary objective is to demonstrate if either GBP or PGB demonstrates superiority over the other in terms of efficacy for the treatment of patients diagnosed with CS. The co-primary outcome is leg pain intensity using a visual analogue scale (VAS) measured at baseline and at weeks 4, 8, 10, 14 and 18. The participants will be asked to rate their average leg pain over the last 24 h on a scale of 10, with zero representing ‘no leg pain’ and 10 representing the ‘worst pain imaginable’ [10].

The co-primary outcome is the Oswestry Disability Index (ODI) [10], measured at baseline and at weeks 4, 8, 10, 14 and 18, to assess disability. The Health Locus of Control Scale (HLOC) will also be used at baseline and at weeks 4, 8, 10, 14 and 18 to assess participants’ decision-making processes because we have identified compliance with these medications as being low [10].

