Participating in PAGPROS is completely voluntary, and participants can stop taking part at any time without explanation or prejudice. Ceasing to participate in PAGPROS may be considered, for example, wherever participants wish to explore the possibility of other treatments, including other medications or interventions (*see above*). In some cases, participants may find that the starting dose of either PGB or GBP, whilst efficacious, produces unwanted SEs [10]. In such cases, a lower dose may be required, at least for a period of time. Because this cannot be accommodated within the current PAGPROS protocol, such patients will be removed from the study, and their data will be analysed as per intention-to-treat (ITT) principles; however, they may still form part of a prospective cohort for parallel study.

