## Discussion

The PAGPROS protocol presents the design and rationale for a double-blind, double-dummy, randomised cross-over trial comparing the efficacy of PGB with GBP in treating CS. Owing to the variability in regular dosage frequency between the medications (PGB twice daily, GBP thrice daily), study medication packs will contain three bottles each, correlating to the dosage times of morning, lunchtime and night, to maintain blinding. Medication packs pertaining to the PGB arm will have placebo incorporated as the lunchtime dose, with all medications being indistinguishable.

Thus, PAGPROS represents the first head-to-head study to determine the relative role of either PGB or GBP in the evidence-based medical management of CS. However, in addition to efficacy, PAGPROS will also determine the frequency and severity of SEs with PGB or GBP. Thus, PAGPROS will determine the ‘efficacy versus SE trade-off’ with each drug and whether differences in compliance rates result in consequences. For example, in a prior study with GBP in treating CS, 31% of patients ceased GBP within 1 week of treatment [10]. Moreover, efficacy was significantly less in those who experienced SEs in that study [10].

In PAGPROS, we will employ the HLOC to assess psychological functioning with PGB or GBP in CS. In particular, PAGPROS will explore the prognosis of each drug relating to questionnaire outcomes relating to patients’ insight into their psychological dysfunction. Thus, PAGPROS may determine deficits and provide information not actually reported as SEs by the patients themselves. This may prove to be an important aspect of the study. For example, a prior prospective cohort study with GBP in treating CS revealed that, of 23 different SE types amongst 53% of patients, more than half could have adversely affected the ability to drive a motor vehicle safely or even to maintain employment [10].

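### The 20% drop-out allowance behind n = 38 has no stated source and is not reconciled with the protocol's own report of 31% stopping gabapentin within a week

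*Protocol article*

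**What the plan says.** **Sample size.** The effect and variability are given as "If the true difference in means of both arms of the study is 0.9 with an SD of 1.2", followed by "we will need to study 30 patients (15 per treatment arm) to reject the null hypothesis with 80% power". The inflation step is "Assuming a 20% drop-out rate, the total sample size will be 38 patients (19 per treatment arm"). No source or reasoning is offered for the 20%.

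**Discussion.** "in a prior study with GBP in treating CS, 31% of patients ceased GBP within 1 week of treatment". The same paragraph adds that efficacy in that study was lower among patients with side effects. The Primary objective and outcome section describes compliance with these drugs as low.

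**Study treatment.** Some patients may do well on the starting dose but need a lower one because of side effects. Of these the section says "such patients will be removed from the study, and their data will be analysed as per intention-to-treat (ITT) principles". Patients who need another pain intervention are also withdrawn. Earlier in the same section, the dosage of either drug "can be amended at any stage in PAGPROS on the basis of efficacy and/or SEs".

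**Data collection, and Data integrity and analysis.** The first outcome after baseline is at week 4, and week 10 is the second baseline. Outcomes are collected by telephone, email or online. Analysis is by intention to treat with last observation carried forward (LOCF); a longitudinal mixed model is named as a possible alternative.

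**The concern.** The 20% has to cover both drugs and both periods up to week 18. The only discontinuation figure in the protocol is higher than that, and it concerns one of the two drugs in its first week. All participants are due that drug, half of them in the first period if the sequences are balanced.

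Stopping a drug need not mean loss of data. Here it is likely to, because the stated rules take patients out of the study when they cannot tolerate the starting dose or need other pain treatment. Two things are then at stake. The number of patients with an observed outcome on both drugs may fall short of the 30 the calculation requires. The loss may also be informative: the patients who leave are those with side effects, and the Discussion reports lower efficacy in such patients and makes the balance of efficacy against side effects an aim of the trial.

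**Working it through.** **Inputs.** Difference 0.9, SD 1.2, 30 evaluable, 80% power, 20% drop-out and 38 in total, all from Sample size. On alpha that section states "The type I error probability associated with this test of the null is 0.05". Sidedness is not given. I take two-sided, because the aim is superiority in either direction: "Our primary objective is to demonstrate if either GBP or PGB demonstrates superiority over the other in terms of efficacy". The 31% comes from the Discussion.

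**Step 1: reproduce the plan's 30.** Paired t-test on the within-patient difference, noncentrality = 0.9 / (SD of difference / √n), n − 2 degrees of freedom.
- If 1.2 is the SD of one measurement, with the two measurements taken as uncorrelated, the SD of the difference is 1.2 × √2 = 1.697. At n = 30, noncentrality = 0.9 / (1.697/√30) = 2.90 and power is 80.1%. This reproduces the stated figure.
- If 1.2 is the SD of the difference, 16 or 17 patients would be enough (n − 1 or n − 2 degrees of freedom). This does not reproduce 30.

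**Step 2: reproduce the 38.** 30 / (1 − 0.20) = 37.5, rounded up to 38. The arithmetic is right; only the 20% is in question.

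**Step 3: put 31% in its place, as if all who stop were lost.**
- Completers: 38 × (1 − 0.31) = 26.2, about 26.
- Power with 26 pairs: noncentrality = 0.9 / (1.697/√26) = 2.70, power 73.7% (73.9% on n − 1 degrees of freedom).
- If 1.2 is the SD of the difference: noncentrality = 0.9 / (1.2/√26) = 3.82, power about 96%.
- Chance of at least 30 completers among 38 (binomial): 66% at 20% loss, 12% at 31% loss.
- Enrolment needed for 30 completers: 30 / 0.69 = 43.5, so 44.

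**Step 4: what ITT with LOCF does with early losses.** A patient removed before week 4 of the first period has only a baseline value. LOCF carries it to both week 8 and week 18, so the drug difference is zero by construction. As an illustration, let a fraction d of all 38 contribute zero and the rest behave as planned:
- mean = 0.9(1 − d); variance = (1 − d) × 1.697² + d(1 − d) × 0.9².
- d = 0.20: mean 0.72, SD 1.56, power at n = 38 about 79%.
- d = 0.31: mean 0.621, SD 1.47, power at n = 38 about 72%.

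This treats every loss as a first-period loss. A patient lost in the first week of the second period would have the week 10 value carried forward instead. That is not a zero difference, but it is not an observed response to the second drug either.

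**The case against.** **The 31% is not a drop-out rate.** This stands. It is cessation of treatment in another study, and the protocol gives neither the dose nor the reasons, nor does it say whether follow-up ended. A reader might infer that 20% and 31% flatly contradict each other. They do not, because they measure different things. What remains is that the 20% is unsourced and not reconciled with the 31%, while the removal rules make the two likely to converge. The dose schedule may also differ from that study's. The protocol says its own ascent is slow enough to reduce side effects, but under Dosages it says a low and slow introduction is not possible.

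**ITT is stated.** This also stands. A reader might infer that removed patients are dropped and ITT is not delivered. The text says their data will be analysed by ITT, LOCF gives each of them a value, and a mixed model could use patients with one period. The narrower point survives: for an early removal, that value is a carried-forward baseline and not a contrast between two observed responses.

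**A larger power loss is not supported.** Applying 31% to each drug gives 38 × 0.69² = 18.1 completers and power of about 56%. The documents give no stopping rate for pregabalin. The product also assumes that tolerance of two related drugs is independent within the same patient. Positive correlation would leave more completers.

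**The dose wording may be consistent.** The lower dose that cannot be accommodated can be read as one below the starting dose, with amendments allowed above it. On that reading most of the apparent conflict with amendment at any stage disappears.

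**Side effects are still recorded.** Weekly monitoring and recording of all adverse events are planned, so information up to removal is kept. The full protocol may also say more about follow-up. The point therefore rests on the stated removal rule and the stated 20%, not on the article's silence.

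**Conclusion.** The point holds in a limited form. The step from 30 to 38 is computed correctly, but its 20% is unsourced and lower than the only discontinuation figure the protocol reports.

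If the 31% became loss, about 26 patients would complete and power would be about 74% instead of 80%. Analysing all 38 with zero differences for the lost gives about 72%. Both figures assume a two-sided 0.05 test and 1.2 as the SD of one measurement, and the completer figure further assumes loss unrelated to the drug difference. If 1.2 is the SD of the within-patient difference, power is not a problem (about 96%), although the stated 30 is then unexplained. The concern about early removals, who give no observed contrast between the drugs, holds under either reading of the SD.

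This is a moderate shortfall that should be addressed. It does not show that ITT has been abandoned or that the trial is badly underpowered.

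**What to change.** 1. Separate stopping study drug from leaving the study. Continue to collect VAS, ODI and side effects by phone or online at the scheduled weeks from everyone randomised, whatever they are taking, unless they withdraw consent to follow-up.
2. Give the basis for the 20%, or state power as a range over 20% to 31% loss (about 80% to 74%), and say whether 1.2 is the SD of one measurement or of the within-patient difference.
3. Reconcile the two statements in Study treatment, on amending the dose and on removing patients who need a lower one, so that it is clear who is removed. No view is taken here on which rule is right.

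The cost is protocol wording, a few extra contacts per affected patient through channels already in use, and a less favourable stated power. No additional patients are needed for these changes. Continued follow-up reduces the bias from losing intolerant patients, but it does not by itself restore 80% power if those who stop show no difference between the drugs. Replacing a 31% loss to keep 30 completers would take 44 patients instead of 38.
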